**Fig. 1 Fig1:**
[figure not shown]
The multi-center’s location for the longitudinal study on responsive feeding in China

The principal institution responsible for the study is the Department of Child, Adolescent Health and Maternal Care, School of Public Health, Capital Medical University located in Beijing.

### Participants and selection criteria

At present, China’s government offers children free and compulsory vaccinations, including the vaccines for Hepatitis B, Bacillus Calmette-Guerin, Diphtheria, Pertussis and Tetanus that are delivered in primary public medical institutions during the first year of life. We plan to recruit 700 women delivering singleton infants who are willing to attend five research centers during regular vaccination days and willing to participate in six rounds of follow-up surveys. We will use each contact opportunity to remind doctors and parents about their next follow-up survey appointment. Inclusion criteria are women: (1) aged 18–50 years with full-term singleton birth; (2) living in the target neighborhood for at least 1 year, (3) can continue visit one of the five study centers to receive healthcare services at least until 12 months after birth. Exclusion criteria are: (1) mothers that delivered twins or multiple birth; (2) premature birth; (3) babies with congenital diseases; (4) maternal mental disorders or difficulty understanding and completing the study questionnaires; (5) known diseases that could affect breastfeeding.

### Sample size calculation

From the perspective of health equity, we designed the study to enroll participants from rural and urban areas. We estimate the sudy sample size based on the different prevalences of breastfeeding in urban an rural areas.

The sample size was calculated using the following formula for comparison of two proportions:
$$ {\mathrm{n}}_{\mathrm{urban}}={\mathrm{n}}_{\mathrm{rural}}=\frac{{\left[{\mathrm{Z}}_{1-\upalpha /2}\sqrt{2\overline{\mathrm{p}}\left(1-\overline{\mathrm{p}}\right)}+{\mathrm{Z}}_{\upbeta}\sqrt{{\mathrm{p}}_1\left(1-{\mathrm{p}}_1\right)+{\mathrm{p}}_2\left(1-{\mathrm{p}}_2\right)}\right]}^2}{{\left({\mathrm{p}}_1-{\mathrm{p}}_2\right)}^2} $$where *n*_urban_ and *n*_rural_ are the sample sizes corresponding to the urban and rural groups, respectively; *Z*_*1-α/2*_ and *Z*_*β*_ are the Z values corresponding to the alpha (*α*) and beta (*β*) error, respectively; *p*_1_ and *p*_2_ are the estimated proportion of breastfeeding rates in urban and rural areas, respectively, while $$ \overline{p} $$ is the average of *p*_1_ and *p*_2_.

According to the China Development Research Foundation (CDRF) 2019 *Report on National Survey of Factors Influencing Breastfeeding*, the prevalence of breastfeeding during the first six months of life in large cities (estimated *p*_1_) and medium/small cities (estimated *p*_2_) was 36 and 23%, respectively. With a statistical power of 90% and a two-tailed significance level of 5%, we estimated that a minimum of 257 participants for each group (urban and rural), should be recruited respectively. Therefore, a sample of 514 are required to observe a 13% difference in the prevalence of breastfeeding between the two groups. Taking into consideration that 25% participants may be lost to follow-up, our goal is to enroll 700 participants.

### Recruitment procedures

Centers’ obstetricians, midwives and/ or experienced nurses will review and screen the information of the women who have delivered within the previous 72 h following the study’s enrollment criteria. The study will then be explained to those mothers who meet the criteria with the help of a leaflet that briefly and clearly explains the study. Enrolled participants will swipe a quick response code (QR code) to provide their web-based informed consent and register into the survey system using the WeChat App. The informed consent form explains in detail the study procedures and includes statements on the benefits and harms regarding study participation. It specifically presents information on potential risk, and confidentiality and privacy protection measures. All participants will be reassured that their participation is voluntary and that they are free to withdraw at any wave of the study without giving any reason, and that their decision to participate or not will not affect the clinical care for them or their infants. The administration of each survey was designed to not exceed 30 min. Before the survey started, all staff received a one-hour on-line training that included a formal assessment to confirm that staff had a full understanding of the project research methods, confidential management of information, and quality control system. The protocol for this study was approved by the Ethics Committee of Capital Medical University (No. Z2019SY001).

### Data collection

The electronic self-administered questionnaires were developed by team members with strong expertise in maternal-child public health nutrition. All data will be collected via an online questionnaire management system (www.wjx.cn) popular and widely used in China, and that is similar to SurveyMonkey®. We developed the electronic version of all the self-administered questionnaires before recruitment started, pretested and released them for participants to fill in on the study’s secure web-based system. Local doctors who are responsible for recruitment will undertake quality control for the survey and will ensure only the eligible participant could access to the survey system. This approach has been successfully implemented in other studies with similar populations in China [28–30]. The specific procedures followed across the six survey waves are shown in Fig. 2. The first survey (wave 1) will be completed within 72 h after delivery on-site under the supervision of a health care provider. Participants can fill out the questionnaires for the remaining five surveys either on-site or at home by clicking the web link forwarded to them.

**Fig. 2 Fig2:**
[figure not shown]
The 6-wave survey procedure of data collection for the multi-center longitudinal study on responsive feeding in China

The timeline and contents of the questionnaire are summarized per study wave in Table 1. Data collected will includes mother’s KAP related to breastfeeding, postnatal depression, emotional regulation and parenting stress; as well as infant’s growth (weight, length) and development status, including cognition. Data on barriers for breastfeeding and RF in general will include self-reported healthcare services access and socioeconomic status.

**Table 1 Tab1:** Timeline of questionnaire application by study wave in the multi-center longitudinal study on responsive breastfeeding in China

Online questionnaire content	Wave 1 (1st survey)	Wave 2 (2nd survey)	Wave 3 (3rd survey)	Wave 4 (4th survey)	Wave 5 (5th survey)	Wave 6 (6th survey)
	within 72 h pp	1 month pp	3 months pp	6 months pp	9 months pp	12 months pp
Informed consent	Mothers	Mothers	Mothers	Mothers	Mothers	Mothers
Socio-demographic information	Both	Both	Both	Both	Both	Both
Knowledge, attitude and practice towards breastfeeding	Mothers	Mothers	Mothers	Mothers	Mothers	Mothers
Infant feeding style questionnaire (IFSQ) [31]	Mothers	Mothers	Both	Both	Both	Both
Edinburgh postnatal depression scale (EPDS) [32]	Mothers	Mothers	–	–	–	–
Emotion regulation questionnaire (ERQ) [33]	Mothers	Mothers	Mothers	Mothers	Mothers	Mothers
Parenting stress index-short form (PSI-SF) [34]	–	–	–	Mothers	Mothers	Mothers
Caregiver reported early childhood development instruments (CREDI) [35], reported by mothers	–	–	Infants	Infants	Infants	Infants

Note: The information of mothers and infants will be collected simultaneously; the content of each questionnaire is detailed in its corresponding area of the methods/ design section. All the scales that used have been translated and pre-tested in Chinese

Abbreviation: pp., postpartum

### Measurement of outcomes, independent variables and covariates

The outcome indicators are based on growth and developmental indicators such as infants’ weight, length, and child development score based on the Caregiver Reported Early Childhood Development Instruments (CREDI) [35].

The key independent variables are the following mother’s RF-related behaviors: mother’s KAP towards breastfeeding including exclusive breastfeeding or not; duration of breastfeeding; pressuring child to eat, restricting what child eats, and responsive styles according to infant feeding style questionnaire (IFSQ) [31]; postnatal depression scores; emotion regulation scores; parenting stress scores.

The co-variates included are based on household socio-demographic data including socioeconomic status and household geographical location and corresponding health center.

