### Socio-demographic and biomedical information of infants

The socio-demographic information of the children will be abstracted from the birth certificate files in wave 1; these will include sex, birth weight, recumbent length, birth date, pregnancy duration, mode of delivery. The data on infant growth will be based on the weight and length measurements that will be conducted by pediatricians when infants visit the study center for vaccination in waves 2–6.

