### Statistical analysis

Descriptive analysis will be performed to describe the socio-demographic characteristic of the participants and to summarize the scale scores of the questionnaires. In order to identify the inequity factors of RF, the crude and adjusted breastfeeding rates for urban or rural residence and the associations between RF and early childhood development outcomes will be estimated with their corresponding 95% confidence intervals (95% CI). Continuous variables will be presented as mean with standard deviation (SD) or median with interquartile range (IQR). After testing for the normality of the distribution means will be compared using Student’s t test or analysis of variance. Categorical variables will be presented as counts with percentages and compared using Person’s χ^2^ test or Wilcoxon rank-sum test between groups, such as urban and rural.

For the cross-sectional analysis of the data, logistic regression and linear regression will be performed to identify barriers and facilitators of RF or infant growth and development, respectively. Interactions among the latent influencing factors will be performed using multivariable analysis to test for potential effect modification taking inequities indicators into account, such as socioeconomic status, psycho-emotional status and maternal health care access. For the longitudinal data analysis, linear mixed effect model or multilevel mixed-effects models will be performed to determine the association between RF and infant growth and development after adjusting for time dependent and static covariates. The statistical significance will be considered as a two-tailed *p* value ≤0.05. All data will be analyzed using Statistical Analysis System (SAS Institute Inc., Cary, North Carolina, USA).

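### The stated covariate list names household and center factors only and leaves out infant sex, birth size, gestation and age, which the growth and CREDI models need and which the study largely collects

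*Protocol article*

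**What the plan says.** In the section Measurement of outcomes, independent variables and covariates, the protocol article sets the outcomes: "The outcome indicators are based on growth and developmental indicators such as infants’ weight, length, and child development score", the score being the CREDI. The same section gives the covariates: "The co-variates included are based on household socio-demographic data including socioeconomic status and household geographical location and corresponding health center".

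The section Socio-demographic and biomedical information of infants lists what is abstracted at wave 1: "these will include sex, birth weight, recumbent length, birth date, pregnancy duration, mode of delivery". For later waves it says: "The data on infant growth will be based on the weight and length measurements that will be conducted by pediatricians". This is done at vaccination visits in waves 2 to 6.

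The Statistical analysis section plans cross-sectional regressions ("For the cross-sectional analysis of the data, logistic regression and linear regression will be performed to identify barriers and facilitators of RF", with infant growth and development as the other target). It also plans a mixed model relating responsive feeding to growth and development "after adjusting for time dependent and static covariates". That phrase names no variable.

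**The concern.** The outcomes are measured on the infant, but no infant characteristic appears in the stated adjustment set. Two things are at stake.

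- **Precision.** Sex, age at measurement and birth size account for part of the spread in weight and length. Leaving them out puts that spread into the residual.
- **Confounding.** Birth size comes before feeding and may influence it. A small infant may be supplemented, pressured to eat or weaned because of size. If so, a feeding coefficient that is not adjusted for birth size mixes the effect of feeding with a difference that existed at birth. The second hypothesis under Aims and objectives is directional (feeding acts on growth and development), so this bears on a main aim.

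The variables are already in the data collection, so the gap lies in the analysis wording.

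**Working it through.** **1. The sections side by side**

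| Variable | Collected? | Named as covariate? | In Statistical analysis? |
|---|---|---|---|
| Socioeconomic status, location, health center | yes | yes | only through the generic covariate phrase |
| Infant sex | wave 1 | no | no |
| Birth weight and birth length | wave 1 | no | no |
| Pregnancy duration | wave 1 | no | no |
| Birth date | wave 1 | no | no |
| Date of each later measurement | not stated | no | no |

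The Statistical analysis section refers to time-dependent and static covariates without listing them. The only definition of the covariates is therefore the sentence in the outcomes section.

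**2. The plan's own figure**

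Inputs from Sample size calculation: p1 = 0.36, p2 = 0.23, mean 0.295, two-sided 5%, 90% power.

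n = [1.960 × √(2 × 0.295 × 0.705) + 1.282 × √(0.36 × 0.64 + 0.23 × 0.77)]² / 0.13² = 257 per group after rounding up.

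The total is 514, and 514/0.75 = 686, close to the 700 planned. The figure reproduces. It concerns breastfeeding prevalence in urban and rural areas, and the article gives no power statement for growth. Its only use here is the number analysed: 700 × 0.75 = 525, or about 262 per group if split evenly.

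**3. Size of the effect (illustration)**

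Let r be the correlation between birth size and later size. The documents do not give it, so I take 0.2 to 0.5. Let d be the difference in birth size between feeding groups in SD units, which is also an assumption, at 0.1 to 0.3.

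- Residual variance removed by adjustment = r².
- Residual SD factor = √(1 − r²).
- Shift in the unadjusted contrast ≈ r × d.

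| r | Variance removed | SD factor | Shift, d = 0.1 | Shift, d = 0.3 |
|---|---|---|---|---|
| 0.2 | 4% | 0.98 | 0.02 SD | 0.06 SD |
| 0.3 | 9% | 0.95 | 0.03 SD | 0.09 SD |
| 0.4 | 16% | 0.92 | 0.04 SD | 0.12 SD |
| 0.5 | 25% | 0.87 | 0.05 SD | 0.15 SD |

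For scale, two groups of 262 detect (1.960 + 0.842) × √(2/262) = 0.24 SD at 80% power and (1.960 + 1.282) × √(2/262) = 0.28 SD at 90%. The largest shift in the table is about half the second figure (0.15/0.28 = 0.54). The smallest is negligible.

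These are single-time-point calculations with no other correlated covariate. They do not carry over directly to a mixed model that already separates variation between infants.

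**The case against.** The best defence is that the covariate sentence is not closed. It uses an inclusive word, the mixed model adjusts for covariates it does not list, and the infant items carry a socio-demographic label: "The socio-demographic information of the children will be abstracted from the birth certificate files in wave 1". On that reading the infant variables may already be meant. The defence shows ambiguity, but it does not supply the variables. The covariate sentence speaks of household data, which on an ordinary reading does not include birth weight, and the section with the infant list is headed as biomedical as well as socio-demographic.

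Second, Participants and selection criteria excludes preterm and multiple births and congenital disease. This narrows the variation in gestation and birth size and so weakens the confounding, gestation most of all. It does not remove variation in birth size among full-term infants.

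Third, every magnitude above rests on assumptions. That stands.

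A reader might also infer several stronger points, which the document does not support:

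- *Growth will be analysed as raw weight and length.* The article names the measurements and gives no analysis scale. Standardisation is a detail commonly left to the full protocol or analysis plan.
- *Exact age is already available.* Birth date is collected, but the article does not say that the measurement date is recorded. The questionnaire date is not a safe substitute: "Participants can fill out the questionnaires for the remaining five surveys either on-site or at home".
- *Feeding and growth are related with no time ordering.* The cross-sectional regressions are same-time analyses, but the article is silent on ordering in the mixed model. Some ordering is built in: Table 1 places the depression scale at waves 1 and 2 and CREDI at waves 3 to 6.
- *Recruitment before and after the pandemic pause will be pooled without adjustment.* The article does not say so.

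**Conclusion.** The point holds in a limited form. The article states a covariate set for infant growth and development that names household and center factors only, while the infant variables it collects are not assigned to any model. That is a stated list that fits its outcomes poorly, and it needs reconciling with the infant data section and the Statistical analysis section. It does not show that the analysts will certainly leave these variables out.

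If the list is followed as written, the loss is 4% to 25% of residual variance for an assumed correlation of 0.2 to 0.5. The possible shift in a feeding contrast is 0.02 to 0.15 SD if feeding groups also differ by 0.1 to 0.3 SD in birth size. The direction and true size of any bias cannot be determined from the documents.

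**What to change.** In Measurement of outcomes, independent variables and covariates, and again in Statistical analysis, add infant sex, birth weight, birth length, gestational age and age at measurement to the covariates of the growth and CREDI models. An equivalent for growth is to analyse age- and sex-standardised z-scores adjusted for birth size. Compute age from the birth date and the visit date, and record the visit date if this is not already done.

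For the second hypothesis, a model relating feeding at an earlier wave to later growth can serve as a sensitivity analysis, because the cross-sectional regressions cannot separate the two directions. Adjusting for the infant's own previous size or score is not required. It is a debatable choice in a mixed model, and it loses outcome waves: CREDI starts at wave 3, so that wave has no prior score. Lagging the parenting stress score, collected only at waves 4 to 6, would leave only waves 5 and 6 as outcomes. A recruitment-period term is not required either.

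The cost is a change of wording, a few extra model terms and, if it is missing, one date field per visit.

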### Socio-demographic data of mothers

Socio-demographics will be collected from wave 1 to wave 6 via the self-administered questionnaires. The information collected in wave 1 will include maternal date of birth, marital status, maternal educational attainment, current employment status, duration of maternity leave, household monthly income, height and weight at beginning of pregnancy, weight gain during pregnancy, pregnancy complications and smoking status during pregnancy. The data on current employment and maternity leave status will be also be collected at waves 2, 3 and 4. The information on date of birth and current employment status will be collected for verification purposes at waves 5 and 6.

### Knowledge, attitude and practice towards breastfeeding of mothers

The data on KAP towards breastfeeding assessed in wave 1 will include source of breastfeeding knowledge, infant feeding patterns, colostrum feeding, formula feeding, exclusive breastfeeding, frequency of breastfeeding or formula feeding. Data will also be collected on difficulties encountered during breastfeeding and if any, to whom the mother turns to for support, intentions with regards to breastfeeding or formula feeding, introduction or feeding of solids, other beverages. Data on infant feeding practice will be collected in waves 2–6. It will include breastfeeding status, frequency of breastfeeding and difficulties encountered during breastfeeding. Mothers no longer breastfeeding will be asked to report when they stopped breastfeeding, frequency, dosage, and duration of formula feeding and other fluids and solids, if any, will also be collected. The reason for introducing and frequency of solid foods consumption will be documented in waves 3–6.

### Feeding beliefs and behaviors measurement: infant feeding style questionnaire (IFSQ)

The IFSQ was designed to measure infant feeding beliefs and behaviors of mothers and infants via estimating latent factors for five feeding styles, namely laissez-faire, restrictive style (RS), pressuring style (PR), responsive style (RP) and indulgent, with 39 questions on maternal beliefs (coded on a 5-point Likert scale: disagree, slightly disagree, neutral, slightly agree, agree) and 44 questions on behaviors (coded on a 5-point Likert scale: never, seldom, half of the time, most of the time, always) [31]. Data for estimating the latent food behavior factors will include in waves 1 and 2: finishing (PR8), cereal (PR12–15) and soothing (PR17,19) for pressuring style; amount (RS4) and diet quality (RS8–11) for restrictive style; and satiety (RP6–7) and attention (RP12) for responsive style. In waves 3–6 data collected will include finishing (PR1–3), cereal (PR11) and soothing (PR16) for pressuring style; amount (RS1–2) and diet quality (5–6) for restrictive style; and satiety (RP1–5) and attention (RP8–11) for responsive style.

### Postnatal depression screening: Edinburgh postnatal depression scale (EPDS)

The EPDS is a 10-item self-reported scale that will be used to screen for postnatal depression [32] in waves 1–2. The mothers in the study will be prompted to choose the response options that best defines the frequency of occurrence over the past 7 days of the different depression symptoms listed. Specifically, they will need to choose either never, occasionally, often and always; and a corresponding value ranging from 0 (never) to 3 (always) will be assigned to each scale item, based on the response option selected. Subsequently, a summative score ranging from 0 to 30 will be computed for each mother. The higher the total scores, the stronger the risk of being depressed. Mothers will be classified as follows: in need for referral if scale scores ≥9; needs more in-depth diagnosis if scale scores ≥13; likely to be in need for psychiatric treatment if the 10th-item (‘the thought of harming myself has occurred to me’) score is ≥1.

### Emotion regulation: emotion regulation questionnaire (ERQ)

The ERQ is designed to assess the capacity for emotion regulation via 10-item statements from the perspective of cognitive reappraisal or expressive suppression [33]. The cognitive reappraisal facet is composed by 6 statements, with the remaining 4 statements focusing on expressive suppression. Each statement is responded with a 7 Likert menu with the item score ranging from 1 to 7; the higher value indicates that the strategy being probed for is being used more frequently emotion regulation. Higher cognitive reappraisal is linked to positive patterns of affect, social functioning, and life satisfaction [36]. By contrast, emotional suppression is associated with negative affect and maladaptive action [37]. The ERQ will be assessed in each wave of the survey to be able to examine the association of maternal emotion regulation with infant feeding practices.

